## Introduction

The use of spinal fusion (SF) procedures has significantly increased over the past decade to stabilize the spine in degenerative, oncologic, and traumatic conditions (1). Despite advancements in spinal surgery, pseudarthrosis remains a concern, occurring in approximately 25–35% of procedures (2–6). Several factors influence fusion rates, including patient characteristics (e.g., age and osteoporosis) and treatment-related aspects (e.g., number of levels treated, use of instrumentation, interbody grafts, and surgical approach) (7). With the increase in aging population and the growing need for multilevel spinal fusion surgery, there is a demand for techniques that enhance SF success rates and reduce pseudarthrosis (8). While iliac crest autograft and local autograft (spinous processes/laminae) are considered the gold standard, their use is limited by supply constraints and associated complications (1, 9). Bone allografts serve as substitutes for autografts and can be combined with Vertebral Bone Marrow Aspirate (vBMA) instead of iliac crest bone marrow aspirate to enhance osteogenic properties (10–12). vBMA is readily accessible in spinal surgery during the preparation for pedicle screw insertion and contains ⁓70% more osteoprogenitor cells—derived from mesenchymal stem cells (MSCs)—than iliac crest aspirates (13, 14). Studies have also shown that MSCs from vBMA exhibit high expression levels of Bone Gamma-Carboxyglutamate Protein (BGLAP), Alkaline Phosphatase (ALPL), and Runt-Related Transcription Factor 2 (RUNX2) genes, which are key regulators of the mineralization process, along with specific Hox gene expression, which influences vertebral morphology (13–15). Furthermore, despite vertebrae being sites of high bone turnover and among the first affected by age-related osteoporosis, the biological characteristics of vBMA remain unaffected by donor age (16, 17). However, the primary limitations of vBMA use in spinal surgery include the lack of a standardized procedure and its liquid nature, which risks diffusion away from the implant site (18).

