Developing an advanced 3D *in vitro* model of SF: the vBMA clot is placed between allograft bone chips and cultured *in vitro* to evaluate cell viability, adhesion, distribution, and colonization of the cells within the vBMA clot in the allogeneic bone chips. Biological, molecular, histological, histomorphometric, and immunohistochemical analyses are performed;Characterizing, through immunoenzymatic assays and molecular techniques, the expression of platelet-derived growth factors, cytokines/chemokines, and osteotropic and angiogenic factors present in the coagulated vBMA can modulate bone formation, healing, regeneration, vascularization, and inflammation. Additionally, biological and molecular analyses are conducted to characterize the morphology, phenotype, and differentiation potential of MSCs present in the coagulated vBMA;Quantifying the antibacterial activity of vBMA can be achieved through microbiological tests using both Gram-positive and Gram-negative bacterial strains, employing microbiological techniques, cell biology methods, and scanning electron microscopy.

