After defining and managing the dataset, bivariate or multivariate analyses are carried out to evaluate relationships between variables. In the case of continuous data, the independent Student’s *t*-test and Wilcoxon rank-sum test are used to compare data between the two treatments for parametric and non-parametric data, respectively. Linear models are applied for regression analysis. In the case of categorical dichotomous data, Fisher’s Exact test or chi-squared test is used to compare proportions between the two treatments, and logistic models are applied for regression analysis. For non-dichotomous categorical data, the Mann–Whitney U-test or the Wilcoxon rank-sum test is used to compare ordered outcomes between the two treatments, and the Ordinal Least Squares, Cumulative Link, or Multinomial Logistic models are applied for regression analysis.

Since the variable of the primary outcome is dichotomous (fusion or no fusion), it is analyzed in relation to age (categorized) and gender through logistic regression models. Additional factors (e.g., follow-up time points) and covariates (e.g., platelet-derived growth factors) influencing spinal fusion may be included in the model. To combine covariates into a multiple logistic regression model, collinearity and predictive power are assessed. The results are reported as odds ratios (ORs) with corresponding 95% confidence intervals (CIs). The primary outcome is also assessed through appropriate stratifications of the population based on the presence or absence of specific comorbidities.

Given the longitudinal nature of FU data (e.g., VAS, ODI, and spinal fusion grading across multiple time points), repeated-measures ANOVA or linear mixed-effects models are applied to assess both within-subject (time) and between-group (treatment) effects, accounting for intra-subject correlation and missing data. This finding allows for a robust evaluation of changes over time and treatment efficacy.

Finally, after defining the most reliable models based on multiple criteria (e.g., Akaike Information Criterion, R^2^), diagnostic tools are used to evaluate model assumptions and identify potential influential observations. The same analysis process is implemented for the other regression models related to secondary outcomes, with appropriate diagnostics applied.

Data collection and statistical analysis are standardized and blinded.

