
## Potential limitations

This study protocol may have several potential limitations. Although a 12-month follow-up period is generally sufficient to assess early fusion and clinical outcomes, a longer follow-up, ideally 24 months, would allow for a more comprehensive evaluation of long-term fusion stability and the durability of clinical benefits. The monocentric design could introduce center-specific biases related to surgical technique and perioperative management, potentially affecting the generalizability of the results. Additionally, while age and sex are considered, other relevant confounding factors, such as comorbidities, smoking status, bone mineral density, and concurrent pharmacological treatments, may not be fully controlled and could influence both radiological and clinical outcomes. Despite standardized imaging protocols, radiological evaluation may still carry a degree of interpretative variability. Furthermore, the heterogeneity of the patient population in terms of baseline pathology and surgical indications may introduce variability in the outcomes. Finally, although the biological composition of the vBMA clot is analyzed, its correlation with individual patient outcomes is not currently planned, which may limit insights into inter-patient variability in biological efficacy.

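### The primary fusion model may take clot growth factors as a covariate, although controls probably have no such values and the limitations section says clot composition will not be related to patient outcome

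*Protocol article*

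**What the plan says.** All references are to the protocol article.

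- **Statistical methods, comparison of arms.** For dichotomous data, Fisher's exact "test or chi-squared test is used to compare proportions between the two treatments". The sample size also rests on a one-tailed Fisher test.
- **Statistical methods, primary outcome.** Fusion is dichotomous, and "it is analyzed in relation to age (categorized) and gender through logistic regression models". This sentence does not name treatment. The text then adds that "covariates (e.g., platelet-derived growth factors) influencing spinal fusion may be included in the model".
- **Statistical methods, choice of model.** "To combine covariates into a multiple logistic regression model, collinearity and predictive power are assessed". Diagnostics follow "after defining the most reliable models based on multiple criteria (e.g., Akaike Information Criterion", with R² as a further example.
- **Statistical methods, missing data.** Missing values may be imputed: singly if very few are missing, otherwise by MICE under missing at random.
- **Outcomes.** The laboratory work characterises "the expression of platelet-derived growth factors, cytokines/chemokines, and osteotropic and angiogenic factors present in the coagulated vBMA".
- **Surgical procedures and interventions.** Group 2 receives allograft chips alone. The aspirate left over after surgery goes to the laboratory, with a pointer to Figure 1, whose caption names the experimental group.
- **Potential limitations.** The clot's biological composition is analysed, but "its correlation with individual patient outcomes is not currently planned".

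**The concern.** A covariate in a between-arm model should be known in both arms and should not be a product of the treatment. The one biological covariate that the plan names appears to fail on both counts. It is assayed in the clot, and the clot is the experimental treatment. The section on scientific relevance also presents growth-factor release as one of the ways in which the clot is meant to act.

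Two things are at stake. First, an adjusted odds ratio from such a model either cannot be computed or depends on control values that nobody measured. Second, one section allows growth factors to be related to fusion patient by patient, while another says that this is not planned. A reader of the results could not tell whether such an analysis had been intended.

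The plan also leaves the adjusted model's covariates to be settled on the trial data, so the adjusted treatment estimate is not fixed in advance.

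**Working it through.** **1. The plan's own sample size.** Inputs from Statistical methods: one-tailed Fisher test, power 0.80, 5% level, control fusion rate 0.70, odds ratio 4.8, equal groups, 20% drop-out.

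- Experimental rate: odds = 4.8 × 0.70/0.30 = 11.2, so the rate is 11.2/12.2 = 0.918.
- The smallest group size with exact power of at least 0.80 is 46 (power 0.802).
- With drop-out: 46/(1 − 0.20) = 57.5, rounded up to 58. This matches the stated 58 per group.

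This comparison uses no covariates, so the issue below does not touch it.

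**2. Complete-case fit with the growth factor.** Assume that growth factors exist only in Group 1. Take the model logit P(fusion) = b0 + b1·treatment + b2·growth factor, with 58 per arm.

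- Patients with all terms observed: 58 experimental, 0 control.
- Among them treatment always equals 1, so its column equals the intercept column. The design matrix has rank 2 of 3.
- Only b0 + b1 and b2 can be estimated. The treatment effect b1 cannot.

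**3. Multiple imputation.** With 58 of 116 values absent, the rule for more than a few missing values would apply. No control value is observed, so the imputation model cannot learn how the factor differs by arm and must carry the Group 1 relation over to Group 2.

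This was simulated with about 300 trials per row, 58 per arm, 20 imputations, control fusion rate 70%, experimental rate 91% at the average factor level, and a one-sided 5% Wald test. The documents give no strength for the factor. The log odds ratios per SD below are assumptions that span a range.

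| Assumed log OR per SD | Median OR, unadjusted → adjusted | Median SE | Power |
|---|---|---|---|
| 0 | 4.71 → 4.57 | 0.55 → 0.58 | 0.93 → 0.91 |
| 0.5 | 3.90 → 3.97 | 0.54 → 0.58 | 0.85 → 0.78 |
| 1 | 3.02 → 2.98 | 0.50 → 0.59 | 0.79 → 0.59 |

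Within each row the odds ratio hardly moves. The cost is precision: power falls by about 2, 7 and 19 points.

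**4. The two statements side by side.** Statistical methods: growth factors may enter a model of each patient's fusion. Potential limitations: relating clot composition to individual outcomes is not planned. Fitting the first is an instance of the second, so both cannot stand. This conflict does not depend on which arm was sampled.

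**5. How many covariates the data could carry.** At 46 evaluable per arm and rates of 70% and 91%, expected non-fusions are 46 × 0.30 + 46 × 0.09 = 13.8 + 4.1 = 17.9. That supports a short list.

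**The case against.** The strongest reply is that the treatment comparison is safe. The logistic sentence concerns age and gender and does not name treatment. The arms are compared by Fisher's exact or chi-squared test, and growth factors only may be added. This largely stands. A reader might infer that the trial's treatment effect becomes inestimable, but the documents do not support that. The problem arises only if the optional covariate is used in a model that also contains treatment. The text does not rule that model out, and it plans to report odds ratios from the logistic models.

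Second, no sentence says that controls are not sampled. The aspiration instruction names no arm, and the laboratory samples are said to come from trial patients generally. This stands too. Absence in all controls is a strong inference from the leftover-aspirate wording and the figure captions, not a stated fact. If both arms were assayed, steps 2 and 3 above would not follow.

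Third, a reader might infer that imputation would badly bias the effect or adjust away the clot's mechanism. Under the stated rule the simulation shows lost precision, not a shifted odds ratio. Large distortion appeared only when control values were set to zero, which the plan does not propose.

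Fourth, a reader might infer serious false-positive inflation from choosing models by AIC. In simulation the best-AIC model rejected only slightly more often than a model fixed in advance, so no inflation figure is claimed. Such selection does not make any effect inestimable either.

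Finally, the Introduction lists "number of levels treated, use of instrumentation, interbody grafts, and surgical approach" among influences on fusion. That does not make the number of levels a required covariate. The plan's covariates are examples, and the final list may sit in an analysis plan that is not shown. Adding levels, keeping age continuous or using penalised likelihood are preferences, not corrections.

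**Conclusion.** The point holds in a limited form. The plan names, for the primary outcome's model, a covariate that is part of the experimental treatment and is probably absent in every control. It also contradicts its own statement that clot composition will not be related to patient outcomes.

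The contradiction is certain from the text. The statistical consequence is conditional on three things: growth factors are measured in Group 1 only, the optional covariate is used, and the model contains treatment. In that case a complete-case analysis gives no treatment estimate. Imputation gives one that rests on extrapolated control values, with a power loss of about 2 to 19 points under the assumed strengths.

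The unadjusted comparison of fusion rates, on which the 58 per group rests, is unaffected. The choice of covariates by predictive power, AIC or R² is a smaller, separate weakness: it leaves the adjusted estimate open, with only a small effect on type I error.

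**What to change.** 1. In Statistical methods, remove platelet-derived growth factors as the example covariate, and state that no clot-derived measure enters a between-arm model of fusion.
2. Limit analyses that relate growth factors to fusion to exploratory work within Group 1, or state that none will be done. Make Statistical methods and Potential limitations agree on this.
3. Fix the covariates of the adjusted treatment-effect model in advance, as a short list of baseline factors known in both arms, and name treatment as a term.
4. Keep selection by predictive power, AIC and R² for exploratory models, and say so.
5. State in which arm or arms the aspirate is taken and assayed, so that the inference above is no longer needed.

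These are wording changes with no effect on the sample size. The one small downside is less freedom to add covariates later.

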### Outcomes

The primary outcome is to compare the two groups regarding the rate and duration of SF. Radiographic assessments are conducted preoperatively and at 1, 3, 6, and 12 months of FUs. To minimize exposure to ionizing radiation, computed tomography (CT) is performed only at 6 and 12 months, alongside x-rays. A diagnostic and interventional radiologist, blinded to group assignments, evaluates CT scans and x-rays, assigning interbody fusion grade according to the Brantigan classification (ranging from A to E, with E indicating the highest fusion rate) (22). The SF rate is analyzed over the FU period, considering variations due to age and gender differences.

The secondary outcomes include evaluating the pseudoarthrosis rate estimated using the Brantigan classification (22) and clinical outcomes. Moreover, since Brantigan (and other similar) classifications are visual qualitative scales affected by a lack of precise quantification, we provided a new quantitative analysis based on density calculated on CT images. The density of the selected region of interest (ROI) has been calculated and reported in Hounsfield Units (HU) for each study (baseline and follow-up controls). ROIs have been positioned within facet joint spaces of all vertebral levels of interest. Differential values in facet joint density have been reported by comparing baseline with follow-up controls to integrate the Brantigan scale (or help in cases of difficult grading selection), offering a quantitative and reliable tool. Measurements were performed using Picture Archive Communication System (PACS) software version 12.2.6.2000019.

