Clinical outcomes include the following:Quality of life improvement was assessed through the VAS (0–10, with higher scores indicating more severe pain), the ODI (0–100, with higher scores indicating greater disability), and the SF-36, a standardized quality of life questionnaire based on patient self-assessment (23–25). These measures are administered at baseline (pre-surgery) and at 1, 3, 6, and 12 months postoperatively. Although patient-reported outcomes such as ODI, VAS, and SF-36 are typically self-reported, a blinded evaluator collected these outcomes to ensure standardization, consistency, and completeness of data across all participants. This approach minimizes potential biases related to symptoms and functioning reporting and enhances the overall reliability of the collected data.Postoperative complications are assessed through medical records, with complications classified as early (major and minor) or late based on their time of onset. Re-operation rates and implant removal were also recorded and analyzed as part of the clinical outcomes, indicating surgical complications and long-term treatment success. The results are analyzed for up to 12-month FUs.Laboratory parameters include routine blood tests, including red and white blood cell counts, platelet count, mean platelet volume, hemoglobin levels, etc., that are collected preoperatively and postoperatively. Additionally, any comorbidities and adverse events are systematically recorded.

Finally, coagulated vBMA from patients enrolled in the RCT is used to conduct several preclinical *in vitro* studies aimed at further investigating its characteristics, biological potential, and anti-inflammatory and antibacterial properties. These studies also evaluate age and gender differences and include an analysis of their interactions. Specifically, clotted vBMA is employed for the following:

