### Statistical methods

The sample size for the trial was calculated through an *a priori* power analysis using G*Power software (version 3.1.9.6, University of Kiel, Germany), considering a power of 0.80 and a confidence level of 95% (one-tailed Fisher’s exact test). The effect size, in terms of odds ratio, was calculated based on spinal fusion literature data (23, 24). Ricart et al. (26) reported spinal fusion rates of 90% in patients treated with autograft + demineralized bone matrix (DBM), compared to 70% in those treated with allograft and bone marrow aspirate (BMA) (OR = 3.9). Slosar et al. (27) reported SF rates of 93% in patients treated with allograft and bone morphogenetic protein (BMP) compared to 73% of those treated with allograft alone (OR = 5.3). Therefore, the effect size was set at an OR of >4.8, assuming a higher SF percentage in the group treated with vBMA clot combined with allogeneic bone chips (>91%) compared to the group treated with allogeneic bone chips alone (<70%). For each treatment group, the minimum number of patients is *n* = 58, including a 20% drop-out rate.

Statistical analysis is conducted using R software and related packages, such as ggplot2, for graphical data representation. A *p-*value of < 0.05 is considered statistically significant. All data are recorded in an electronic dataset containing continuous variables (e.g., age, growth factor expression, and bacterial time kill results), categorical nominal variables (e.g., gender, diagnosis, and treatment), and categorical ordinal variables (e.g., Brantigan SF classification, VAS score, and ODI score). A univariate analysis should be conducted to determine the distribution, central position (e.g., mean and median), and dispersion (e.g., variance, standard deviation, and interquartile range [IQR]) of quantitative variables. For qualitative variables, frequency distributions are reported. Continuous variables with skewed distributions are transformed and assessed to achieve normality.

To prevent information loss and the introduction of potential selection bias, missing values may be imputed. In cases with very few missing values, a single imputation method is applied; otherwise, a multiple imputation method is applied, providing valid inferences under the missing at random (MAR) assumption. To perform multiple imputations, the Multivariate Imputation by Chained Equations (MICE) R package is used.

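### The longitudinal analysis of VAS and ODI leaves repeated-measures ANOVA open and names no baseline covariate or treatment-by-visit term; fixing one baseline-adjusted mixed model would gain precision at no cost

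*Protocol article*

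**What the plan says.** Under Outcomes, VAS, ODI and SF-36 are secondary clinical measures: "The secondary outcomes include evaluating the pseudoarthrosis rate estimated using the Brantigan classification (22) and clinical outcomes". Their schedule has five visits, one of them before surgery: "These measures are administered at baseline (pre-surgery) and at 1, 3, 6, and 12 months postoperatively".

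Under Statistical methods, the repeated measurements are introduced with "Given the longitudinal nature of FU data (e.g., VAS, ODI, and spinal fusion grading across multiple time points", and the analysis is "repeated-measures ANOVA or linear mixed-effects models are applied to assess both within-subject (time) and between-group (treatment) effects". The same sentence says that this is done while "accounting for intra-subject correlation and missing data".

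Missing values are covered earlier in that section. Imputation is allowed, by a single method when very few values are missing; "otherwise, a multiple imputation method is applied, providing valid inferences under the missing at random (MAR) assumption".

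For VAS and ODI the article names no baseline covariate, no treatment-by-visit term and no target visit. For the fusion model, by contrast, it does go to covariate level: age, gender, follow-up time point and platelet-derived growth factors are all mentioned.

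**The concern.** Three things are fixed badly.

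- **Two different models stay open.** Repeated-measures ANOVA and a linear mixed model treat an incomplete patient differently. The claim about missing data is true of a likelihood-based mixed model under missing at random. It is not true of classical repeated-measures ANOVA, which needs every visit from every patient. The trial plans for 20% drop-out, so this matters.
- **The pre-surgery score has no stated role.** In a randomised comparison of VAS or ODI it is usually a strong predictor of the later scores. Leaving it out as a covariate does not bias the comparison, but it enlarges the standard error.
- **The contrast is not named.** Time and treatment effects are listed, but not their interaction. If the pre-surgery visit were among the responses, the treatment main effect would average in a visit at which randomisation makes the expected difference zero.

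At stake is the chance of detecting a real difference in pain, disability or quality of life in a trial whose sample size was set for fusion alone.

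**Working it through.** **The plan's own figure.** The only sample size stated is for fusion: 58 per arm including 20% drop-out, "considering a power of 0.80 and a confidence level of 95% (one-tailed Fisher’s exact test". With a control rate of 0.70 and an odds ratio of 4.8 (experimental rate 0.918), exact one-sided Fisher power first reaches 80% at 46 per arm (0.801), and 46/(1 − 0.20) = 57.5, rounded up to 58. The figure reproduces. It says nothing about VAS or ODI, but it supplies the number evaluable: 58 × 0.80 = 46.4, taken as 46 per arm.

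**Assumptions (none given in the documents for VAS or ODI).** Equal SDs at all visits, set to 1; the same correlation r between any two visits, r = 0.4, 0.5, 0.6; a constant post-surgery effect d = 0.4 SD; two-sided 0.05; normal approximation, power = Φ(z − 1.96), with z = effect / √(2V/46).

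**Variance V per patient and effect for each analysis:**

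- A. Treatment main effect with the pre-surgery visit as a fifth response: effect (0 + 4d)/5 = 0.8d = 0.32; V = (1 + 4r)/5.
- B. Mean of the four post-surgery visits, unadjusted: effect 0.40; V = (1 + 3r)/4.
- C. The same mean, adjusted for baseline: effect 0.40; V = (1 + 3r)/4 − r².

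| r | A: V, power | B: V, power | C: V, power | Patients needed, B relative to C |
|---|---|---|---|---|
| 0.4 | 0.520, 57% | 0.550, 73% | 0.390, 87% | 1.4 |
| 0.5 | 0.600, 51% | 0.625, 68% | 0.375, 88% | 1.7 |
| 0.6 | 0.680, 46% | 0.700, 63% | 0.340, 91% | 2.1 |

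Example at r = 0.5. For B, z = 0.4/√(2 × 0.625/46) = 2.43, power 68%. For C, z = 0.4/√(2 × 0.375/46) = 3.13, power 88%. The ratio is 0.625/0.375 = 1.7.

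**12 months alone, r = 0.5.** Unadjusted: V = 1, z = 0.4/√(2/46) = 1.92, power 48%. Baseline-adjusted: V = 1 − 0.25 = 0.75, z = 2.22, power 60%.

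B against C is the fair comparison, because it takes the reading kindest to the plan. A applies only if the pre-surgery score is a response. All rows use 46 per arm, so none of them includes a further loss from dropping incomplete patients.

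**The case against.** The best defence is that this is a condensed article. Covariates, interaction terms and target visits for secondary outcomes commonly sit in the statistical analysis plan, which is not shown. Nothing in the text rules out baseline adjustment, and a linear mixed model, the right class, is already one of the two options. This stands as a limit on severity. It does not dispose of the point, because the article states a choice between two models and makes a claim about missing data that is wrong for one of them unless imputation is added.

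Three stronger readings are tempting, and the documents do not support them.

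- **That the plan dilutes the effect with the pre-surgery visit.** The models are applied to follow-up data, and Outcomes distinguishes baseline from follow-up. Analysis A is possible under the wording but not stated; on the post-surgery reading there is no dilution. Quoting 51% against 88% as the cost would set the worst reading against the best alternative.
- **That incomplete patients are dropped.** No complete-case analysis is stated, and multiple imputation by chained equations is provided for. The loss arises only if repeated-measures ANOVA is chosen and the optional imputation is not used.
- **That VAS and ODI fall back on a t-test.** The article classes them among "categorical ordinal variables (e.g., Brantigan SF classification, VAS score, and ODI score", and assigns rank tests and ordinal models to such data. The unadjusted 12-month figure above is therefore a benchmark, not a description of the plan.

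**Conclusion.** The point holds as a matter of precision and of an unfixed model. The article permits an analysis of VAS and ODI that ignores the collected pre-surgery score, and it credits repeated-measures ANOVA with a handling of missed visits that the method lacks without imputation. Even if only post-surgery visits are analysed, baseline adjustment of the same four-visit mean raises power from about 68% to 88% at r = 0.5 (73% to 87% at r = 0.4; 63% to 91% at r = 0.6). These figures rest on an assumed constant effect of 0.4 SD, equal SDs, equal correlations and 46 per arm. The size of the gain depends on the correlation; its direction does not.

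A reader might infer that the clinical comparisons are biased. Under randomisation, leaving out the baseline covariate costs precision and does not bias the estimate. Bias from drop-out would need the unimputed complete-case route, which the documents allow but do not state. The outcomes are secondary, and the primary fusion result is unaffected.

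**What to change.** In Statistical methods, delete repeated-measures ANOVA as an option. Analyse VAS, ODI and SF-36 with a linear mixed model on the 1-, 3-, 6- and 12-month scores, with baseline score, treatment, visit and treatment-by-visit as terms and the within-patient correlation modelled. Report the baseline-adjusted treatment difference averaged over the four post-surgery visits and at 12 months. State that the 12-month contrast alone has less power (about 60% at r = 0.5 under the assumptions above). Restrict the statement that missing data are accounted for to this mixed model, under missing at random.

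The cost is a wording change in the protocol or analysis plan. All the scores are already scheduled, so no patients, visits or measurements are added.
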